**FIGURE 3 F3:**
[figure not shown]
Protocol for recruitment selection and initial screening and baseline data collection.

The study received ethics approval from Sydney Adventist Health (SAH) human ethics research committee (HREC) (approval number 2019-032). All experiments are carried out in accordance with the approved ethics guidelines.

### Eligibility and recruitment

The study consists of 40 PD patients (20 male + 20 female) recruited *via* media advertisements on TV and local media.

Due to the remote (virtual) nature of this trial, only PD participants categorized as Hoehn and Yahr Stage I-III during ON periods, and willing to have a carer present during all assessments and treatment sessions are included. Consent forms are signed by hand, and both emailed and posted back (see Figure 4 for overview of recruitment process).

**FIGURE 4 F4:**
[figure not shown]
Protocol for treatment and assessments.

### Inclusion criteria

•Females and males aged 59–85 years•Diagnosed with Idiopathic PD (by United Kingdom Brain Bank Criteria) with Modified Hoehn and Yahr Stage I–III during ON periods•≥3 weeks of stable anti-PD medications•Sufficient space (around 9 m^2^) to be able to perform motor assessments•Suitable and sufficiently fast home-based internet connection for uninterrupted video calls and video conferencing•Knowledge (self or carer) of using a phone and/or tablet applications on either IOS or Android platforms•Attendance of a “carer” during each Zoom meeting and during all participant treatment sessions

Exclusion criteria – Participants will be excluded from the study if they:

•Are not capable of self-care•History of significant psychotic episode(s) within the previous 12 months•History of suicidal ideation or attempted suicide within previous 12 months•Take potentially photosensitizing medications, in particular imipramine, hypericum, phenothiazine, lithium, chloroquine, hydrochlorothiazide, or tetracycline•Have history of structural brain disease, active epilepsy, stroke, factors affecting gait performance and stance unrelated to PD, such as due to severe joint disease, orthopedic injuries, weakness, peripheral neuropathy with proprioceptive deficits, severe peripheral vascular occlusive disease, severe musculoskeletal disorders, uncorrected vision, vestibular problems or other acute illness or severe condition that would:-Preclude the use of PBM therapy-Place the patient at risk during evaluation of their PD, or-Interfere with the evaluation of their PD•Are currently participating in other clinical trials, including treatment of PD•Are currently using any form of self-administered light therapy•Have evidence of severe and unstable dysautonomia•Have significant cardiac disease⚬Cardiac interventions (in the past 3-months)⚬Unstable arrhythmias (in the past 3-months)⚬Diagnosis of cardiac dysautonomia

### Randomization

Following virtual screening and informed consent, 40 participants will be randomized into two groups and then allocated into a treatment or sham group *via* an independent research administrator and thereafter identified *via* an anonymous SN (serial number). To reduce the chance of participants inadvertently realizing that they are in the sham group, the HREC approved that the participants be informed there are four groups: active infrared, inactive infrared, active red + infrared, inactive red + infrared. Group 1 will receive active treatment and Group 2 will receive a sham helmet, which is identical in appearance. Participants will be instructed on helmet use by a trained technician *via* Zoom video communication.

By intention there will be equal numbers of males and females in each group. While it is well-known that gender differences effect human disease including PD, little research has been performed into the different gender responses to PBMt (Liebert et al., 2022). Therefore, the efficacy and tolerability outcomes of PBMt transcranial delivery will be subject to sub analysis based on gender.

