## Methods and analysis

### Trial design

The study is a 24-week, two-arm, triple blinded randomized placebo-controlled trial evaluating the safety and effectiveness of the “PDNeuro” Helmet (see Figures 1, 2) compared with a sham helmet device. Treatment will consist of PBMt to the head six times per week for 12 weeks (see Figure 3), with Group 1 (the active group) receiving 12 min of infra-red and 12 min red LED, and Group 2 (the sham group) receiving sham treatment for 24 min. After the initial 12 weeks, the sham patients will be given the active treatment for 12 weeks while the active treatment group will have a 12 weeks washout period and then be re-assessed in 12 weeks (see Figure 3). Outcome measures will be collected by the study investigators that have received specialized training in assessment and data collection.

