### Intervention

The participants will be mailed their “PDNeuro” or sham helmet with all treatment to be self-administered at home in the presence of their carer. Study participants will be provided with detailed written and visual instructions on correct helmet fitment and treatment protocol. This will be supplemented with a Zoom video consultation with a trained technician and scientist to ensure correct device fitment and operation. During this Zoom consultation the helmet will be viewed from the frontal, sagittal, and transverse plane to ensure correct fitment. Participants will be subsequently monitored on a weekly basis with a compulsory consultation with the same trained research personnel to ensure continued correct fitment of the study device and adherence to the study protocol. In addition, all participants will be encouraged to reach out to the research team outside of these monitorisation periods for any trial related queries *via* either phone or email which are monitored 24-h per day, 7-days per week.

The PBMt intervention will consist of six 24 min-treatment sessions per week for 12 weeks (see Figure 3). Participants in Group 1, the active treatment group, will receive transcranial light treatment with a “PDNeuro” LED Helmet device with 20 LED stimulus sites, each having one IR (810 nm) LED and one Red (630–670 nm) LED. Average optical power for the IR LED (810 nm) is 52 mW and for the RED LED (630–670 nm) 27 mW. Treatment dose will consist of 0.052 W × 720 s to total 37.44 joules for IR and 0.027 W × 720 s to total 19.44 joules for red. Therefore, with 37.44 and 19.44 joules delivered over 20 diodes a total of 1,137 joules will be administered per session.

Participants in the placebo/sham group (Group 2) will receive the same apparent treatment as Group 1, except that they will be “treated” with sham transcranial LED devices that deliver no light. After the 12 weeks the placebo group will be offered a further 12 weeks of treatment with the active “PDNeuro” Helmet.

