#### Primary outcome measurements

Safety of the “PDNeuro” Helmet device, MDS-Unified Parkinson’s Disease Rating Scale (MDS-UPDRS) modified Part 3 and social experiences and difficulties as measured with the Parkinson’s disease-specific quality of life questionnaire, the PDQ-39.

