### Advantages and limitations

This is a triple blinded RCT designed to minimize bias and maximize the validity of any differences observed between the treatment and sham groups. While the triple blinding of this RCT is an advantage, restrictions resulting from SARS-CoV-2 affected the initial protocol, creating several limitations. Due to restrictions in Australia during the conception of this trial, it was not feasible to invite participants into a clinic setting for in-person intervention and assessments due to government regulations at the time. Furthermore, the increasing rate of infections and hospitalizations during this period meant that movement of research staff and participants to and from a clinic/hospital location would introduce an increased risk of potential COVID-19 infection. Therefore, the decision was made to pivot the study to a home-based trial to minimize as much person-to-person contact as possible, and to mitigate any risk of infection to our vulnerable population.

The scientific/clinical validity and feasibility of conducting our RCT remotely had been assessed prior to commencement of the study. For example, the UPDRS assessment used for the RCT has been shown to be clinically valid when conducted remotely (Schneider et al., 2020). Indeed, the feasibility, reliability, and value of implementing remote telemedicine/video-based assessments for Parkinson’s disease patients for both research (Tarolli et al., 2020) and ongoing healthcare (Cubo et al., 2020) have been previously evaluated and deemed valid. Furthermore, all outcome measures will be assessed by medical professionals (physicians, nurses, physiotherapists) who have been trained to conduct clinical assessments in Parkinson’s disease patients, with supervision of leading neurologist to ensure assessment accuracy and reliability.

The resulting limitation is that treatment is delivered unsupervised with only a carer present. This means that there is a reliance of self-reporting and participant honesty that the “PDNeuro” Helmet is being applied correctly for the duration of the treatment period. Assessments are also being recorded *via* video communication and although cameras are effective in providing visual feedback it is possible that fine tremors may be missed and reliance of carers to manipulate the camera and give good visual observation may present a challenge.

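### The four-group cover story protects blinding in the sham arm only: if the active helmet's red light is seen, it identifies active treatment, so the triple blind is not secured for the self-completed PDQ-39.

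*Protocol article*

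**What the plan says.** Trial design in the protocol article states: "The study is a 24-week, two-arm, triple blinded randomized placebo-controlled trial". Advantages and limitations repeats the claim ("This is a triple blinded RCT") and presents it as a strength.

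On the light itself:
- Trial design has the active group "receiving 12 min of infra-red and 12 min red LED".
- Intervention gives "six 24 min-treatment sessions per week for 12 weeks", with one red (630–670 nm) and one infra-red (810 nm) LED at each of 20 sites.
- Intervention describes the control as "sham transcranial LED devices that deliver no light".

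On masking, the Randomization section says the sham helmet looks the same as the active one. It adds a cover story, approved by the ethics committee, under which "the participants be informed there are four groups: active infrared, inactive infrared, active red + infrared, inactive red + infrared". The stated purpose is to lower the chance that sham participants work out that they are on sham.

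On who is exposed and who reports: participants treat themselves at home, with a carer present at every session. The primary outcomes include "social experiences and difficulties as measured with the Parkinson’s disease-specific quality of life questionnaire, the PDQ-39", which the PDQ39 section describes as self-administered. PDSS is self-assessed and the carer keeps a diary; both are secondary outcomes. The abstract names participant and carer reports within its main indicator of efficacy. Data collection states that the investigators who collect outcomes are blinded.

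**The concern.** Light at 630–670 nm is in the visible band. An identical housing matches the helmets when they are off, but the described outputs differ when they are on: red light from one, none from the other. The cover story is the only other masking device described, and its logic is one-sided. A dark helmet remains ambiguous. A helmet seen to glow red does not, because only one of the described groups would produce that.

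If the glow is seen, belief about treatment differs between arms in a way tied to allocation. Outcomes that depend on belief, namely PDQ-39, PDSS and the diary, could then differ between arms without any device effect, and the difference would be reported as triple-blind evidence. The results are meant to inform a larger trial, so an unmeasured failure of blinding would carry forward.

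**Working it through.** **1. Confirm the red exposure.** Inputs from Intervention: 0.052 W (infra-red) and 0.027 W (red), 720 s each, 20 sites.

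- Infra-red: 0.052 × 720 = 37.44 J per LED. Red: 0.027 × 720 = 19.44 J per LED.
- Session total: 20 × (37.44 + 19.44) = 1,137.6 J, which agrees with the stated 1,137 J.
- So red light runs for 720 s = 12 min per session. Over 6 × 12 = 72 sessions this is 72 × 12 = 864 min.

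**2. What a participant can deduce.** Take the four groups as told, with equal weight (assumption).

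| Group as told | Red light expected? | Active? |
|---|---|---|
| Active infra-red | No | Yes |
| Inactive infra-red | No | No |
| Active red + infra-red | Yes | Yes |
| Inactive red + infra-red | No | No |

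- P(active | red light seen) = 1/1 = 100%.
- P(active | no red light) = 1/3 = 33%.

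In fact every active participant receives red light and no sham participant does. Among those who see or fail to see it, belief in active treatment is therefore 100% in one arm and 33% in the other.

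**3. Illustration of the consequence.** The documents give no expectation effect, so shifts of 0.2, 0.3 and 0.5 SD are assumed. There is no device effect, 20 per arm (40 in two groups, taken as equal), and a two-sided 5% test. The nominal chance of a significant result favouring the device is 2.5%.

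*Comparison of two means.* Chance = Φ(d × √(20/2) − 1.96).

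- d = 0.2: Φ(0.632 − 1.96) = 9%
- d = 0.3: Φ(0.949 − 1.96) = 16%
- d = 0.5: Φ(1.581 − 1.96) = 35%

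*Between-arm comparison of improvers.* The threshold is the half-SD change in Statistical analysis. With baseline to week-12 correlation r (assumed 0.5 to 0.8), the SD of change is s = √(2(1 − r)) in baseline SD units. The improver rates are p0 = 1 − Φ(0.5/s) on sham and p1 = 1 − Φ((0.5 − d)/s) on active. With p̄ the mean of p0 and p1, the chance is Φ{[p1 − p0 − 1.96√(2p̄(1 − p̄)/20)] / √([p1(1 − p1) + p0(1 − p0)]/20)}.

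| r | p0 | p1 at d = 0.2 / 0.3 / 0.5 | Chance favouring device |
|---|---|---|---|
| 0.5 | 0.309 | 0.382 / 0.421 / 0.500 | 7% / 11% / 23% |
| 0.7 | 0.259 | 0.349 / 0.398 / 0.500 | 9% / 15% / 34% |
| 0.8 | 0.215 | 0.318 / 0.376 / 0.500 | 11% / 20% / 47% |

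Statistical analysis describes chi-square comparisons of improvers between time points. The between-arm version is used here because bias between arms is what blinding guards against.

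**The case against.** The strongest objection is that the article nowhere says the glow is seen. The LEDs treat the scalp from inside a helmet, the helmet figures are not available in the text reviewed, and Intervention asserts that sham treatment appears the same as active. This stands as far as it goes: visibility is an inference. It rests on a visible wavelength at 20 sites, a helmet handled by the wearer, an observer at every session, and no mention of shielding, eye covering or a sham light. The assertion of like appearance does not settle the matter, because the same sentence makes the absence of light the exception.

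A participant might also take the inactive red + infra-red group to mean a helmet that lights up without effect. Nothing in the article suggests participants are told this, and the real sham is dark.

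Three stronger readings are tempting, and the article does not support them:

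- *Every active participant is unblinded.* This holds only if the light is seen.
- *Outcome assessors are unblinded.* At the fitting consultation "the helmet will be viewed from the frontal, sagittal, and transverse plane to ensure correct fitment", and the same staff check in weekly. But no text says the LEDs are lit on camera or that these staff rate outcomes, and Data collection states that outcome collectors are blinded.
- *The false-positive risk is larger still.* An ANCOVA with baseline correlation 0.7 to 0.8 would give higher figures than those above, but the article plans no ANCOVA.

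It is also fair to say that an article may leave a treatment-guess questionnaire to the full protocol. Its absence is not the fault. The fault is a triple-blind claim that the described masking does not secure.

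**Conclusion.** The concern holds in conditional form. From the text alone, the described cover story can conceal allocation in the sham arm only: red light, if seen by participant or carer, points to active treatment with certainty, while its absence leaves a one-in-three chance of being active. The triple-blind claim is therefore not secured for PDQ-39, PDSS and the carer's diary.

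The size of any resulting bias is unknown. Under the assumed shifts of 0.2 to 0.5 SD, the chance of a false finding for the device rises from 2.5% to between 9% and 35% on means, and to between 7% and 47% on half-SD improvers. These figures are illustrations, and the conclusion does not depend on them. It depends on one assumption, that the glow can be seen in use, which the trial can test cheaply.

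A reader might infer that PDQ-39 must lose its primary status. That does not follow. It is a trade-off for the investigators, since keeping PDQ-39 with a stated limitation also answers the point.

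**What to change.** 1. At the week-12 assessment, before any helmet is returned or swapped, record from participant, carer and assessor the guessed allocation, the reason for the guess and any light seen. Report a blinding index by arm.
2. Unless the red light is shown to be unobservable in use, replace the triple-blind label with *sham-controlled, outcome-assessor-blinded to week 12*. Report PDQ-39, PDSS and the carer's diary as open to expectation bias, and give the assessor-rated modified MDS-UPDRS Part 3 more weight in interpretation.
3. Keep the helmet out of view and bar talk of lights during outcome assessments.

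The cost is one short questionnaire at an existing visit, a scripted instruction, and a more modest blinding claim.

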### Intervention

The participants will be mailed their “PDNeuro” or sham helmet with all treatment to be self-administered at home in the presence of their carer. Study participants will be provided with detailed written and visual instructions on correct helmet fitment and treatment protocol. This will be supplemented with a Zoom video consultation with a trained technician and scientist to ensure correct device fitment and operation. During this Zoom consultation the helmet will be viewed from the frontal, sagittal, and transverse plane to ensure correct fitment. Participants will be subsequently monitored on a weekly basis with a compulsory consultation with the same trained research personnel to ensure continued correct fitment of the study device and adherence to the study protocol. In addition, all participants will be encouraged to reach out to the research team outside of these monitorisation periods for any trial related queries *via* either phone or email which are monitored 24-h per day, 7-days per week.

The PBMt intervention will consist of six 24 min-treatment sessions per week for 12 weeks (see Figure 3). Participants in Group 1, the active treatment group, will receive transcranial light treatment with a “PDNeuro” LED Helmet device with 20 LED stimulus sites, each having one IR (810 nm) LED and one Red (630–670 nm) LED. Average optical power for the IR LED (810 nm) is 52 mW and for the RED LED (630–670 nm) 27 mW. Treatment dose will consist of 0.052 W × 720 s to total 37.44 joules for IR and 0.027 W × 720 s to total 19.44 joules for red. Therefore, with 37.44 and 19.44 joules delivered over 20 diodes a total of 1,137 joules will be administered per session.

Participants in the placebo/sham group (Group 2) will receive the same apparent treatment as Group 1, except that they will be “treated” with sham transcranial LED devices that deliver no light. After the 12 weeks the placebo group will be offered a further 12 weeks of treatment with the active “PDNeuro” Helmet.

### Outcome measures

Due to the broad clinical signs and symptoms of PD, a range of outcome measures were selected to determine functional improvement (Table 1). Many PD clinical rating scales have been developed since the 1960s that assess both motor and non-motor functions (Ramaker et al., 2002) and all outcome measures to be used in this study have been validated for use in PD remotely (Abdolahi et al., 2013; Stillerova et al., 2016). The primary outcome measures will be conducted and recorded using a combination of self-reported assessment and visual assessment obtained *via* Zoom video link. Outcome measures will be supervised, and data will be collected *via* specialist examiners and physiotherapists all trained in conducting each assessment. Outcome measures will be obtained at baseline, 12-week and 24-week intervals (see Figure 3).

**TABLE 1 T1:** Outcome measurements.

Primary outcome measurements	Data collection tools
1. Safety of PDNeuro helmet device	24-h access to health personnel Weekly [or as needed] technical meetings
2. Motor assessment	MDS-UPDRS [Modified Part 3 Motor component]
3. Social experiences and difficulties	PDQ39
**Secondary outcome measures**	
1. Mobility	TUG [non-cognitive]
2. Cognition	MoCA
3. Writing task	Repeated sentence writing to assess letter size
4. Sleep habits	Parkinson’s disease sleep scale (PDSS)
5. Carer’s diary	Qualitative assessment of care-givers thoughts

#### Primary outcome measurements

Safety of the “PDNeuro” Helmet device, MDS-Unified Parkinson’s Disease Rating Scale (MDS-UPDRS) modified Part 3 and social experiences and difficulties as measured with the Parkinson’s disease-specific quality of life questionnaire, the PDQ-39.

#### Secondary outcome measurements

1.Movement mobility (TUG [non-cognitive])2.Cognition (MoCA)3.Writing task (assess writing size)4.Sleep habits self-assessment (PDSS sleep scale)5.Carer’s diary of daily living

##### UPDRS

The primary motor measure chosen is the motor assessment (Part 3) of the UPDRS as it is one of the most common movement assessment outcomes used in PD (Ivey et al., 2012), and demonstrates high internal consistency and inter-rater reliability while showing moderate construct validity (Rodriguez-Blazquez et al., 2017).

Furthermore, the UPDRS assessment has been shown to be clinically valid when conducted remotely (Schneider et al., 2020). Indeed, the feasibility, reliability and value of implementing remote telemedicine/video-based assessments for Parkinson’s disease patients for both research (Tarolli et al., 2020) and ongoing healthcare (Cubo et al., 2020) have been previously evaluated and deemed valid.

Sixteen of the eighteen items from the UPDRS motor were included. Rigidity was excluded as this is unable to be determined without manual assessment. As well, postural stability was not performed due to the potential risk of falling if performed without adequate supervision. In the UPDRS all items are scored on a scale from 0 (normal) to 4 (severe), and total scores obtained from the sum of the corresponding item scores, stage the severity of PD. These scores are to be collected using video link with attention being paid to positioning the camera and participant to ensure clear vision. The carer will be required to manipulate the camera to ensure that the participant is clearly visible. All assessors are trained in the administration of the UPDRS assessment tool to maximize the outcome measure.

##### PDQ39

It is well-documented that quality of life (QOL) plays an important role in patient self-efficacy, is instrumental for independent living and, in chronic conditions such as PD is frequently greatly impaired (Megari, 2013). The questionnaire tool PDQ39 is a self-administered questionnaire that assesses PD specific quality of health during a specific time-period. It assesses across eight life dimensions: mobility, ADL’s, emotional well-being, stigma, social support, cognition, communication, and bodily discomfort (Hagell and Nygren, 2007). The PDQ39 will be administered by the patient during the same three time points: pre-treatment, following 12 weeks and 6 months post trial commencement.

